#### Study site randomization

The study will be conducted within a large integrated health system in the Northeast of the USA. Because the number of study sites for this pilot is relatively small, simple unrestricted randomization may not be sufficient to ensure balance between study conditions. Pairing of EDs would improve balance but may reduce study power and is not recommended for small numbers of clusters [88]. Therefore, we will use a minimization procedure to ensure overall balance on three important covariates: annual ED census, location (urban/suburban), and AUDIT-C positive rate. A computerized algorithm will be used to identify all possible allocations that meet the balancing constraints and one of the allocations will be randomly selected [89]. A data analyst not associated with the study will conduct this procedure to minimize bias. Study sites and data analysts will be blinded to the study condition.

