### Aim 3: Examine the feasibility, acceptability, and preliminary effectiveness of the implementation strategy

#### Design

In line with recommendations pertaining to the scope and target outcomes of pilot studies for implementation trials [83–85], the main goal of this pilot trial is to assess the (1) feasibility (i.e., perceptions among ED clinical staff members that the implementation strategy can be successfully used), (2) acceptability (i.e., perceptions among ED clinical staff members that the implementation strategy is agreeable, palatable, or satisfactory), and (3) and preliminary effectiveness of the implementation strategy. We will operationalize our effectiveness outcome as “reach” (i.e., proportion of eligible patients that enroll in the text intervention), which is a key outcome recommended in the implementation science literature [83, 85–87]. The design is a mixed method, two-armed, study in 4 EDs (2 assigned to the new implementation strategy vs. 2 implementation as usual control). Qualitative and quantitative measures will be collected and analyzed simultaneously and merged—qualitative data will provide context to and explanation of the quantitative results in a complimentary way, representing a QUAL + QUAN structure that gives equal emphasis to both types of data [65].

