#### Study conditions

##### Implementation strategy condition

Through virtual and in-person meetings, the internal/external facilitation team will support sites in utilizing the implementation strategy developed in aim 2 for 7 months: 2 months to prepare policies/workflows for offering the text intervention to patients and 5 months actively supporting implementation of offering the text intervention.

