##### Control condition

In control “implementation as usual” sites, no facilitation or implementation strategies will be provided. Controls will receive (1) an informational session on the text intervention during grand rounds/staff meetings and (2) flyers to provide patients with intervention enrollment information. In both conditions, it will be emphasized that any patient who screens positive on the AUDIT-C (as per site protocol in the EHR) are appropriate [34, 35].

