##### Feasibility and acceptability

Feasibility and acceptability of the implementation strategy among staff in the 2 intervention sites will be measured by two 4-item validated measures: the Acceptability of Intervention Measure (AIM), and Feasibility of Intervention Measure (FIM) (e.g., the implementation strategy seems easy to use; the implementation strategy meets my approval) [67]. We will also adapt these measures to assess patients’ views on feasibility and acceptability of the text-messaging intervention to provide context to the effectiveness/reach outcomes.

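### The protocol says study sites and data analysts are blinded, but the two intervention EDs cannot be; blinding is feasible only for a separate analyst of reach

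*Protocol article*

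**What the plan says.** The aim 3 section on study site randomization makes two separate statements. On who performs the allocation: "A data analyst not associated with the study will conduct this procedure to minimize bias". On blinding: "Study sites and data analysts will be blinded to the study condition". The second carries no qualification as to which sites, which analysts or which outcome.

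The Design section gives the split of the four EDs: "2 assigned to the new implementation strategy vs. 2 implementation as usual control". In the intervention arm, "Through virtual and in-person meetings, the internal/external facilitation team will support sites", with 2 months of preparing policies and workflows followed by 5 months of active support. In the control arm, "no facilitation or implementation strategies will be provided"; those sites get an informational session and flyers.

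Under Feasibility and acceptability, "acceptability of the implementation strategy among staff in the 2 intervention sites will be measured" with two four-item scales. The Staff subsection of the data collection procedures sends the staff survey to the 2 intervention EDs only, and takes its staff interviews from them too, at 20 per ED.

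**The concern.** A blinding statement tells readers which biases the design guards against. This one names two groups, and the rest of the article contradicts it for the intervention sites and for anyone who analyses their staff data.

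Reach is the one outcome compared between arms. It is counted from health records and the text platform, but staff behaviour shapes both parts of the proportion. The numerator depends on staff offering the programme, and the denominator on AUDIT-C screening being completed in the same EDs. A reader told that sites were blinded would set aside the possibility that knowing one's arm affected either. The Discussion says that preliminary effectiveness, together with feasibility and acceptability, will feed the decision to progress to a fully powered trial, so the statement bears on how far the reach result can be trusted for that decision.

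**Working it through.** No arithmetic beyond counting applies. The check sets the blinding sentence against what each group will see and do under the plan.

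**Intervention EDs (2 of 4).** The facilitation team "will support sites in utilizing the implementation strategy developed in aim 2 for 7 months" (2 + 5 = 7). The contact is overt: meetings, policy and workflow changes, then active support. Staff are later asked whether the implementation strategy is acceptable and feasible, and chairpersons are asked to pick interviewees who know how it was implemented. Staff cannot rate a strategy without knowing they received it. The blinding claim fails for both of these sites.

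**Control EDs (2 of 4).** They know they received a session and flyers. Whether they know this is the control condition depends on what they are told about the other arm. The article does not say, so their blinding is neither shown nor excluded.

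**Handlers of staff data.** The staff survey covers 2 of 4 EDs and the staff interviews number 2 × 20 = 40, all in the intervention arm. Anyone who works with these data and can see which ED they came from knows that ED's arm. With only four EDs, the other two are then controls by elimination. The patient survey and patient interviews do not have this property, because patients are drawn from enrollees generally and, for the interviews, from all 4 EDs.

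**Analyst of reach.** Reach needs only counts of AUDIT-C-positive patients and enrollees. The text platform gives each site its own enrolment code, and nothing prevents recoding the sites and labelling the arms neutrally before analysis. An analyst who receives only that file and has no part in facilitation or the staff data can stay blinded.

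**Where the streams meet.** The Design section plans simultaneous collection and analysis of qualitative and quantitative measures, followed by merging, and the Analysis section repeats the merging. At that point anyone who sees the combined material can infer the arms. Analyst blinding for reach can therefore hold only up to the merge.

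| Group | Blinding to condition |
|---|---|
| 2 intervention EDs and the facilitators | Not possible |
| 2 control EDs | Undetermined; at most unaware of another arm |
| Handlers of staff survey or interview data | Not possible for the EDs concerned |
| Separate analyst of reach | Feasible with masked codes, until merging |

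**The case against.** The other side has several good points.

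- *A reader might infer that analyst blinding is impossible.* The documents do not support that. Nothing says that one person analyses both the reach file and the staff data, and a reach analyst with masked codes can be blinded exactly where the arms are compared. The details of masking are also something an article may leave to a fuller document, so their absence is not the fault here. What remains is that the sentence covers all data analysts, which cannot be true of those handling staff data from one arm.
- *A reader might infer that all four sites are necessarily unblinded.* Only the two intervention EDs certainly are. Knowing what one receives is not the same as knowing that it is the control condition.
- *A reader might infer that the staff feasibility and acceptability ratings are biased for want of blinding.* They are not shown to be. They are perceptions of a strategy the raters have used, collected in one arm and summarised descriptively. There is no between-arm comparison for blinding to protect.
- *Staff acting differently because they are supported is largely the intended effect.* The Background calls facilitation the active ingredient. This stands: open allocation is inherent in such a trial and is not a design flaw. It does not rescue a sentence saying that the sites are blinded.
- *The sentence may have meant allocation concealment.* The preceding sentence already deals with the conduct of allocation, and this one speaks of blinding to condition. If concealment was meant, the wording still needs correcting.
- *Reach is counted from records and compared with a prespecified z-test*, so knowledge of arm has little room to colour its measurement. That is true of the counting. It does not extend to the offering and screening that generate the counts.

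**Conclusion.** The unqualified blinding statement is wrong for the 2 intervention EDs and for anyone handling staff data from those EDs. It is undetermined for the 2 control EDs and achievable for a separate reach analyst. This is an error in a stated property of the design, not in the choice of design, and correcting it alters no estimate, test or sample size.

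The consequence is moderate. If the statement is carried into the report, it would credit the reach comparison with a protection it lacks. The documents give no basis for a numerical size of any resulting bias, and none is claimed.

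The conclusion assumes that facilitation is delivered as described and that staff data stay identifiable by ED or are known to come from the intervention arm, as the sampling plan implies.

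**What to change.** 1. Delete the claim that study sites are blinded.
2. State that allocation is open to intervention sites, facilitators and those handling staff survey or interview data.
3. Say what control sites are told about the existence of another arm.
4. Limit the blinding claim to the analyst of reach, who works from masked arm and site codes and completes the reach comparison before it is merged with the staff data.
5. Report the lack of site blinding as a limitation when interpreting reach.

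Step 4 does not require staff data to be withheld. They can be analysed in parallel by other people, which respects the simultaneous mixed-methods plan; only the merge waits. The order should be stated alongside that plan in the Design and Analysis sections.

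The cost is a few sentences and one data-masking step.

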#### Study conditions

##### Implementation strategy condition

Through virtual and in-person meetings, the internal/external facilitation team will support sites in utilizing the implementation strategy developed in aim 2 for 7 months: 2 months to prepare policies/workflows for offering the text intervention to patients and 5 months actively supporting implementation of offering the text intervention.

##### Control condition

In control “implementation as usual” sites, no facilitation or implementation strategies will be provided. Controls will receive (1) an informational session on the text intervention during grand rounds/staff meetings and (2) flyers to provide patients with intervention enrollment information. In both conditions, it will be emphasized that any patient who screens positive on the AUDIT-C (as per site protocol in the EHR) are appropriate [34, 35].

#### Text-messaging intervention

The text-messaging intervention to be implemented in this pilot trial [29] includes daily texts tailored to individuals’ responses to brief enrollment and check-in assessments (e.g., drinking goals, self-efficacy). Just-in-time support is also provided (e.g., text “temp” for support to manage a craving to drink). An RCT testing this intervention found 94% retention of participants over 12 weeks, and reductions in the number of heavy drinking days in groups that received active messages (vs. assessment only), with the greatest effect for just-in-time adaptive tailoring. To enroll in the intervention, participants text a number (e.g., REDUCE to 55753) and then receive a welcome message that will prompt them to complete the enrollment assessment. We selected this particular texting intervention for implementation in this study because in a recent meta-analysis it was the only study that had positive outcomes and met all criteria for low bias [90]. Furthermore, it has three key ingredients recommended by the broad text-messaging intervention literature: theory-driven, evidence-based, and adaptively tailored.

#### Data sources and measures

##### Effectiveness/reach

Effectiveness will be examined by calculating how many patients were eligible (positive AUDIT-C) based on EHR data and the proportion who enrolled in the intervention as collected by the text platform. Demographics will also be collected from the EHR and text platform to examine differences in characteristics between who was eligible based on AUDIT-C score and who enrolled. In the text platform, each study site will have a unique enrollment text code number, allowing for tracking of patients that enrolled by site and when they enrolled, demographics, and responses to the intervention tailoring questions (e.g., drinking patterns, self-efficacy, motivation). We anticipate there will be ~5000 UAU eligible patients identified during the study trial period based on (1) sites’ current census, (2) current screen positive rates, and (3) screening completion rates based on our previous evaluations in this integrated health system.

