#### Data collection procedures

##### Patients

A random sample (*n* = 250) of adult patients who screen positive for UAU and enroll in the text intervention will be invited via text message to participate in a survey on the intervention’s feasibility and acceptability 1 month after enrolling in the intervention. A link will be sent to participants via the text-messaging platform for them to participate in the online survey, review informed consent study information sheet, and receive a $15 e-gift card for their participation.

We will also invite 10 patients to participate in qualitative interviews from each of the 4 EDs with a question at the end of the survey inquiring if they are interested; we will then follow up by phone to schedule. A verbal consenting procedure will be conducted by the interviewer along with an information sheet provided to the patient.

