#### Analysis

The same procedures described in aim 1 will be used to analyze qualitative data for aim 3. For the reach/effectiveness quantitative data, we will calculate a proportion for each study condition (e.g., numerator: # of patients in control or intervention sites who enrolled in the intervention; denominator: # of patients with positive AUDIT-C) and use *z*-tests for independent proportions [93] to examine whether control and intervention sites differ significantly. We will also use *z*-tests to examine differences in demographics between those eligible and enrolled to determine whether there are gender or racial disparities. For these proportional analyses [94], to achieve 80% power, a sample size of at least 300 in each condition is needed (total of 600) to detect a 10% difference in proportions with significance level of *p* = .05. For the feasibility/acceptability staff and patient survey data, we will calculate descriptive statistics for each. We will triangulate this quantitative data with the qualitative data by merging the results. No identifying information will be maintained by the study team for any staff or patients; all participants will be identified with a participant ID.

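### The reach numerator (enrolments under a site-wide text code) is not guaranteed to be a subset of its denominator (AUDIT-C-positive patients in the EHR)

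*Protocol article*

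**What the plan says.** Under Aim 3, Design, the effectiveness outcome is reach, the "proportion of eligible patients that enroll in the text intervention". The Effectiveness/reach section builds it from two systems. The denominator comes from "calculating how many patients were eligible (positive AUDIT-C) based on EHR data". The numerator is "the proportion who enrolled in the intervention as collected by the text platform". The only key that the section describes is at site level: "each study site will have a unique enrollment text code number, allowing for tracking of patients that enrolled by site and when they enrolled".

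The Text-messaging intervention section describes enrolment as started by the participant: "To enroll in the intervention, participants text a number", followed by a welcome message and an enrolment assessment. No check of AUDIT-C status is mentioned. The Control condition section gives control EDs an information session and "flyers to provide patients with intervention enrollment information". It adds that in both arms staff will be told that AUDIT-C-positive patients are the appropriate ones.

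The Analysis section counts in the numerator the patients at an arm's sites who enrolled, without restricting it to AUDIT-C positives. It divides by the number with a positive AUDIT-C and compares arms with a z-test for independent proportions. It also states: "No identifying information will be maintained by the study team for any staff or patients". The patient survey is nevertheless to sample "adult patients who screen positive for UAU and enroll in the text intervention".

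**The concern.** A proportion, and a z-test on proportions, require everyone in the numerator to belong to the denominator. Here the two counts come from separate systems, and the plan states nothing that joins them at patient level.

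Under the Aim 1 quantitative section, screening can be deferred (for example for acuity or intoxication) or refused. Such a patient can still text the code but has no positive AUDIT-C in the EHR. The same applies to a screen-negative patient, or to anyone else who is given the code.

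Reach is the pilot's only effectiveness outcome. It is tested for significance and, according to the Discussion, feeds the decision on a larger trial. The comparison of enrolled with eligible patients by gender and race also loses its meaning if some enrollees were never in the eligible set. The survey frame of enrollees who screened positive has the same gap, because the plan does not say how the platform would know who they are.

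**Working it through.** **The plan's own figures.** The article gives no reach value to reproduce. Its one related figure is the sample size: 300 per condition for a 10-point difference, 80% power and p = .05. The base rate is not stated. A two-sided pooled calculation gives 294 per arm for 20% v 30% and 199 for 10% v 20%, so 300 is plausible under some base rates. The point here does not depend on it.

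**Numerator and denominator compared**

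| Element | Source | Restricted to AUDIT-C positive? |
|---|---|---|
| Definition of reach | Aim 3, Design | Yes |
| Denominator | EHR (Effectiveness/reach; Analysis) | Yes |
| Numerator | Text platform, by site code (Effectiveness/reach; Analysis) | Not stated |
| Act of enrolling | Text to a number (Text-messaging intervention) | No check described |
| Patient-level link | None described; study team keeps no identifiers (Analysis) | No |

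**Effect on one arm.** Let N be the eligible patients, E the eligible patients who enrol, and X the enrolments by people outside N. True reach is E/N and observed reach is (E + X)/N. With q = X/(E + X), E + X = E/(1 - q), so observed reach = true reach/(1 - q).

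- q = 10%: 1/0.90 = 1.11
- q = 30%: 1/0.70 = 1.43

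**Effect on the arm contrast when there is a true effect.** Assumed true reach is 10% control and 20% intervention. All values of q are assumed.

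| q control | q intervention | Observed control | Observed intervention | Difference |
|---|---|---|---|---|
| 30% | 10% | 0.10/0.70 = 14.3% | 0.20/0.90 = 22.2% | 7.9 points |
| 20% | 20% | 0.10/0.80 = 12.5% | 0.20/0.80 = 25.0% | 12.5 points |
| 10% | 30% | 0.10/0.90 = 11.1% | 0.20/0.70 = 28.6% | 17.5 points |

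The true difference is 10 points throughout. Even equal q distorts the absolute difference, although it leaves the ratio of the two arms at 2.

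**Effect when there is no true difference.** True reach is 10% in both arms. The article expects about 5000 eligible patients, taken here as 2500 per arm (an assumed equal split). A pooled z-test is used and clustering is ignored. The arm with the larger q is listed first.

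| q | Observed reach | z at these values | Chance of p < .05 |
|---|---|---|---|
| 10% v 0% | 11.1% v 10.0% | 1.28 | 25% |
| 20% v 0% | 12.5% v 10.0% | 2.80 | 80% |
| 30% v 10% | 14.3% v 11.1% | 3.37 | 92% |

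For the last row, the pooled proportion is 0.127 and the standard error is sqrt(0.127 × 0.873 × 2/2500) = 0.0094, so z = 0.0317/0.0094 = 3.37. Exchanging the arms reverses the sign.

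**The case against.** The strongest reply is that the intended quantity is clear and consistent. Design speaks of eligible patients, Analysis counts patients rather than visitors, and the survey is drawn from enrollees who screened positive. On that view only the mechanism of confirmation is missing, and a journal article may leave that to the full protocol.

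Part of this stands: the definition is sound and the mechanism may exist elsewhere. But the article does more than stay silent. It fixes the numerator's source, a site-level key, an open enrolment route and the absence of identifiers with the study team. Followed literally, these do not deliver the stated definition. The survey wording presumes that screen status is known but does not say how.

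A reader might go further and infer three things that the documents do not support:

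- **That ineligible enrolments could never be removed.** The identifier statement binds only the study team. The health system or the platform might match records, and the platform already collects demographics and drinking-pattern responses.
- **That reach is certainly inflated, and more so at control EDs because of flyers.** The flyers are described as being for patients, the intervention arm's workflow is still to be designed in Aim 2, and both arms receive the same message about who is appropriate. Neither the size nor the direction of any imbalance is known.
- **That the reported figure is definitely not a proportion.** It may turn out to be one; the plan does not ensure it.

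That this is a pilot of preliminary effectiveness lowers the stakes but does not remove them, since reach is tested and informs progression.

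**Conclusion.** The point holds in a limited form. As written, nothing in the plan guarantees that enrolments counted by the text platform belong to the AUDIT-C-positive patients in the denominator. Any that do not would inflate reach by 1/(1-q). An unequal q between arms would bias the contrast in either direction and could create a difference where none exists.

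The figures above rest on assumed values of q and of true reach, and the significance results also on 2500 eligible patients per arm and no clustering. They show that moderate imbalances would matter; they do not show that such imbalances will occur. Bias by arm is a possibility left open, not a demonstrated fact. The issue should be settled before enrolment starts, because the information needed to confirm eligibility is hard to recover afterwards.

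**What to change.** In Effectiveness/reach and in Analysis, restrict the numerator to enrollees confirmed as AUDIT-C positive at that ED, and state how this is confirmed.

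1. **Preferred:** the health system matches enrolments to its own records and returns only a de-identified yes/no flag. This keeps the commitment that the study team holds no identifiers.
2. **If that is not feasible:** add items to the existing enrolment assessment on being a patient at that ED, having been screened there, and the AUDIT-C. State that self-report may misclassify some patients and will miss those who skip the assessment. AUDIT-C answers alone would not be enough, because unscreened or deferred patients could still qualify.
3. **Report** all other enrolments separately by ED. Show the unrestricted count only as enrolments per eligible patient, labelled as a ratio, in a sensitivity analysis.
4. **Use the same confirmation** to define the survey frame and the comparison of enrolled with eligible patients.

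The cost is a wording amendment plus either a matching step by the health system or a few extra items, with slight respondent burden and a slightly lower reported reach. The stated sample size does not change, because only the definition of the outcome is affected.
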